### Objectives

The primary objective of our study is to evaluate the efficacy of an early postoperative home-based strength training protocol — to assess whether it can improve patient functional outcomes at 3 months and 1 year following surgery. The secondary objectives are the feasibility of the presented protocol for all elective THA patients and its safety.

Our study also aims to assess patient satisfaction with enhanced targeted physiotherapy and to prepare a new standardized rehabilitation protocol with videos that will be effective, safe, and accessible to all THA patients.

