#### Sample size calculation

A power calculation was performed based on a clinically significant difference in gait speed of 0.10 m/s on the 4- or 10-m walk (10 MW) test using data from Perera et al. [32]. Based on a substantial meaningful change of 0.10 m/s between the interventional and control groups and standard deviation of 0.28 m/s, with a significance level of 5% and a power of 80%, a needed sample size of 124 patients in each group was estimated (248 patients in total). All patients from surgeons, participating in the study, will be assessed for eligibility. A total of 124 patients in each hospital will be randomized according to the procedure described above on a 1:1 ratio, so that there will be 62 patients in group A and group B in both hospitals.

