
### Outcome measures

The primary outcome of the study is the efficacy of the chosen protocol, measured by physical tests. These comprise the 10 MW test, the 8-foot Up and Go (8UG) test, and isometric muscle strength. Secondary outcomes are the patient questionnaires, which will be used to draw conclusions about patient satisfaction and the feasibility of the protocols, and consistent recording of any adverse effects.

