Before any statistical analysis, data will be tested for normal distribution using the Kolmogorov–Smirnov test (K–S test). With normally distributed variables, the analysis of variance for repeated measures (AnovaRM) with two factors (time × group) will be employed. It will test the differences in the effects of two different exercise protocols. AnovaRM will be used to analyze between-group differences in the score changes among all time points, represented by preoperative measurements (on admission to the hospital) and measurements 1, 3, and 12 months postoperatively. Afterwards, the initial AnovaRM, post hoc tests with AnovaRM (time × group) with two time points will be performed. Differences between all pairs of time points will be analyzed. Additionally, the paired samples *t*-test to test for in-group differences in the score changes between the pairs of time points and the independent samples *t*-test for between-group comparisons at the same time point will be calculated. The bivariate Pearson correlation will be calculated for testing the relationships between variables representing relative changes in the results between two different time points (e.g., post-treatment/baseline) for each group separately. To test the reliability of maximal voluntary isometric contraction measurements and the 8UG test, we will use the intraclass correlation coefficient (ICC) with the two-way mixed-effects model with absolute agreement. Data will be presented as the arithmetic mean and standard deviation. In the case of a non-normal distribution, data will be presented as the median and interquartile range, and nonparametric tests will be used respectively for comparisons of dependent and independent groups. Instead of AnovaRM, the nonparametric marginal model (nparLD, R-statistics) [47] will be used. T-tests for dependent and independent samples will be changed with Wilcoxon matched-pair signed-rank test and Mann–Whitney *U* test, respectively. The Pearson correlation will be substituted with the Spearman rank correlation. Adverse effects comparison among the two groups will be made by using the chi-square test. We will consider a *P* value less than 0.05 as significant for all measures and use a 95% confidence interval (CI). A significance level (alpha) of 0.05 will be tested with a two-tailed test.

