## Discussion

We have had good experiences with the standard exercise protocol, so we anticipate that the majority of the patients from both groups will have better performance at 3 months and 1 year after surgery compared to at baseline. All patients should also have higher scores on patient satisfaction questionnaires at 3 months and 1 year after surgery than at baseline. We expect patients in the intervention group to achieve better results in physical tests and maximal voluntary isometric contraction measurements compared to patients in the control group. With respect to other studies, we predict the largest differences at the 3rd postoperative month. We would like to provide evidence that home-based strength and sensory-motor training is safe and easy to understand for the majority of patients and is applicable to all THA patients.

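### The safety objective is served by a chi-square difference test alone; if adverse effects are uncommon, a non-significant result could not support a safety conclusion

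*Protocol article*

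**What the plan says.** Under Objectives, the protocol article states: "The secondary objectives are the feasibility of the presented protocol for all elective THA patients and its safety". Outcome measures lists "consistent recording of any adverse effects" among the secondary outcomes. Under Data management and analysis, the between-group method is given in one sentence: "Adverse effects comparison among the two groups will be made by using the chi-square test". The general rules that follow are "We will consider a *P* value less than 0.05 as significant for all measures and use a 95% confidence interval (CI") and "A significance level (alpha) of 0.05 will be tested with a two-tailed test". The confidence interval is promised for all measures but not attached to any safety quantity. The Discussion says the authors would like to provide evidence that "home-based strength and sensory-motor training is safe and easy to understand for the majority of patients".

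The sample size of 124 per group comes from walking speed only: "Based on a substantial meaningful change of 0.10 m/s between the interventional and control groups and standard deviation of 0.28 m/s".

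Safety information is also used elsewhere. Training compliance says that diary entries (adverse effects, pain scores, reasons for missed sessions) will inform conclusions on safety. Data monitoring says that recorded adverse effects will be discussed with the thesis review panel. Neither section gives a method for comparing the arms.

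**The concern.** The aim and the named tool do not match. A two-sided test of no difference is built to detect a difference. When it fails to reject, it gives no measure of how large an excess of harm is still compatible with the data. That information comes from an interval for the difference between arms.

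The mismatch matters most when few patients are affected. The test then has little power, and the chi-square approximation itself becomes poor because expected cell counts fall below 5. At stake is a secondary objective, but one the authors link to a standardised programme meant for all hip replacement patients. A safety statement resting on a non-significant P value would not tell the reader what had been ruled out.

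**Working it through.** **1. The plan's own figure.** Inputs from Sample size calculation: difference 0.10 m/s, SD 0.28 m/s, two-sided 5%, power 80%.

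n per arm = 2 × SD² × (1.960 + 0.842)² / difference² = 2 × 0.0784 × 7.849 / 0.01 = 123.1, rounded up to 124.

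The stated 124 per group is reproduced. Nothing in this calculation concerns adverse effects.

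**2. Power of the named test for adverse effects.** The article gives no adverse-effect rate, so the control risks below are assumptions, taken from 1% to 20% to show the range. With x and y affected patients among n = 124 per arm, and t = (x + y)/(2n):

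X² = ((x − y)/n)² / (t(1 − t) × 2/n), significant if X² > 3.841.

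Exact power is the sum of the two binomial probabilities over all significant pairs (x, y). The last column is the risk ratio detectable with 80% power, by the normal approximation.

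| Assumed control risk | Power, doubling | Power, tripling | Risk ratio detectable at 80% |
|---|---|---|---|
| 1% | 8% | 18% | 8.6 |
| 2% | 13% | 35% | 5.3 |
| 5% | 32% | 77% | 3.2 |
| 10% | 61% | 98% | 2.3 |
| 20% | 94% | >99% | 1.8 |

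At 5% or below, a doubling would usually be missed. A tripling would usually be missed at 1% or 2%, but not at 5%. At 10% and above, both would more often be found than missed.

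**3. What a non-significant result leaves open (illustrative counts).** Suppose 8 of 124 (6.45%) are affected in the intervention arm and 3 of 124 (2.42%) in the control arm.

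- t = 11/248 = 0.04435, so X² = 0.0016259 / (0.04435 × 0.95565 × 2/124) = 2.38 and P = 0.12.
- The Wilson limits are 3.31% to 12.22% and 0.83% to 6.87%.
- Newcombe lower limit: 4.03 − √((6.45 − 3.31)² + (6.87 − 2.42)²) = −1.4 points.
- Newcombe upper limit: 4.03 + √((12.22 − 6.45)² + (2.42 − 0.83)²) = +10.0 points.

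The test reports no significant difference, while an excess of up to 10 percentage points remains compatible with the data.

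Equal counts show how this depends on frequency. The 95% score interval for the risk ratio is 0.18 to 5.6 with 2 versus 2 affected, 0.35 to 2.9 with 6 versus 6, and 0.61 to 1.6 with 25 versus 25.

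**4. Sparse counts.** Take 4 versus 0 affected; the expected count is 2 per arm.

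- Uncorrected chi-square: X² = (4/124)² / (0.01613 × 0.98387 × 2/124) = 4.07, P = 0.044.
- Fisher's exact test: the probability that all four fall in one named arm is (124 × 123 × 122 × 121)/(248 × 247 × 246 × 245) = 0.061. Doubling for two sides gives P = 0.12.

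The same data fall on opposite sides of 0.05 according to the method.

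**The case against.** A reader might infer that the authors will treat P > 0.05 as proof of safety. The article does not say so. The Discussion sentence is an aspiration, is limited to most patients, and sets no decision rule. A statement about most patients could rest partly on observed proportions within the intervention arm.

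A reader might also infer that the test will generally miss a doubling or tripling of harm. That does not follow. The article gives no rate, and its capture is broad: any adverse effect, recorded through diaries, phone calls and questioning at each visit. If 10% to 20% of controls are affected, power is 61% to 94% for a doubling and at least 98% for a tripling. The statement in Data monitoring that no major side effects requiring discontinuation of the study are expected concerns major events only, so it does not show that adverse effects as a whole will be few.

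The plan also has more than a bare P value. It promises a 95% CI for all measures, states an intention-to-treat analysis, and provides for diary-based and panel review. A fuller analysis plan, not shown, may supply patient-level definitions and interval methods.

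All of this stands and limits the point. What it does not answer is that the article chooses a comparison method for a stated objective, and that method cannot deliver the conclusion sought. At any event rate, a non-significant P value does not say what excess has been excluded. The promised interval would do so, but the text does not connect it to the adverse-effect comparison.

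**Conclusion.** The point holds in conditional form. The one between-group method named for adverse effects is a difference test, in a trial sized only for gait speed, while the authors hope to provide evidence of safety. If affected patients are uncommon (assumed control risk about 5% or less), power for a doubling is 8% to 32%, and a non-significant result could not support a safety conclusion. With sparse counts the P value also depends on which test is used.

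The figures rest on assumed control risks, 124 analysed patients per arm, one count per patient and the uncorrected chi-square test. At assumed control risks of 10% to 20% the power problem largely recedes, though the need for an interval remains. The documents do not support the stronger readings that harm would be missed whatever its frequency, or that the authors have committed to reading P > 0.05 as safety. This is a change worth making to a secondary analysis; it does not affect the primary comparison.

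**What to change.** In Data management and analysis, replace the chi-square sentence with text to this effect: the number of patients with at least one adverse effect will be compared between arms as randomised, using the risk difference with a 95% confidence interval suited to small counts (for example Newcombe's); the safety conclusion will be based on the largest excess that this interval excludes, and not on P > 0.05; any accompanying P value will come from Fisher's exact test when expected counts are below 5.

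This applies the 95% CI and the intention-to-treat principle that the plan already states. It needs no new data and no more patients. The cost is a few lines of analysis and a more cautious safety statement, especially if events prove rare.

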### Data monitoring

Instead of a data monitoring committee (DMC), the presented study is supervised by a doctoral thesis review committee. It is composed of 3 members, whose names are available on request. The corresponding author is obliged to present the study design to the panel before starting the enrollment and to present the interim results and finally conclusions of the study. An interim analysis will be made after the completion of the patient recruitment, at which time the results will also be presented to the panel and any adverse effects recorded will be discussed. Given the existing data from the previous studies, we do not expect any major side effects requiring discontinuation of the study, except that it may be necessary to discontinue the protocol in individual patients.

## Discussion

We have had good experiences with the standard exercise protocol, so we anticipate that the majority of the patients from both groups will have better performance at 3 months and 1 year after surgery compared to at baseline. All patients should also have higher scores on patient satisfaction questionnaires at 3 months and 1 year after surgery than at baseline. We expect patients in the intervention group to achieve better results in physical tests and maximal voluntary isometric contraction measurements compared to patients in the control group. With respect to other studies, we predict the largest differences at the 3rd postoperative month. We would like to provide evidence that home-based strength and sensory-motor training is safe and easy to understand for the majority of patients and is applicable to all THA patients.

### Future directions

The aim of our project is to design a safe, affordable home-based strength and sensory-motor training program for all THA patients that can integrate well with the existing rapid recovery protocol in our hospitals.

## Trial status

Patient recruitment for our study commenced in January 2018 in the General Hospital Novo mesto and in April 2018 in the Valdoltra Orthopedic Hospital and is on-going at the time of the manuscript submission. The expected time of recruitment completion was June 2021, but was postponed due to COVID-19.

## Data Availability

The datasets used and analyzed during the current study are available from the corresponding author upon reasonable request.

## Abbreviations

THA: Total hip arthroplasty
PRT: Progressive resistance training
IG: Intervention group
CG: Control group
HHS: Harris Hip Score
SF-36: 36-Item Short Form Health Survey
OA: Osteoarthritis
LOS: Length of stay
1-RM: 1-Repetition maximum
10MW: 10-M walk
8UG: 8-Foot Up and Go
TUG: Timed Up and Go
ASA: American Society of Anesthesiologists
VAS: Visual analog scale
ICC: Intraclass correlation coefficient
